## Abstract

**Background:**

Access for endovascular repair of abdominal aortic aneurysms (EVAR) is obtained through surgical cutdown or percutaneously. The only devices suitable for percutaneous closure of the 20 French arteriotomies of the common femoral artery (CFA) are the Prostar™ and Proglide™ devices (Abbott Vascular). Positive effects of these devices seem to consist of a lower infection rate, and shorter operation time and hospital stay. This conclusion was published in previous reports comparing techniques in patients in two different groups (cohort or randomized). Access techniques were never compared in one and the same patient; this research simplifies comparison because patient characteristics will be similar in both groups.

**Methods/Design:**

Percutaneous access of the CFA is compared to surgical cutdown in a single patient; in EVAR surgery, access is necessary in both groins in each patient. Randomization is performed on the introduction site of the larger main device of the endoprosthesis. The contralateral device of the endoprosthesis is smaller. When we use this type of randomization, both groups will contain a similar number of main and contralateral devices. Preoperative nose cultures and perineal cultures are obtained, to compare colonization with postoperative wound cultures (in case of a surgical site infection). Furthermore, patient comfort will be considered, using VAS-scores (Visual analog scale). Punch biopsies of the groin will be harvested to retrospectively compare skin of patients who suffered a surgical site infection (SSI) to patients who did not have an SSI.

**Discussion:**

The PiERO trial is a multicenter randomized controlled clinical trial designed to show the consequences of using percutaneous access in EVAR surgery and focuses on the occurrence of surgical site infections.

**Trial registration:**

NTR4257 10 November 2013, NL44578.042.13.

## Background

Percutaneous endovascular abdominal aortic aneurysm repair (pEVAR) has been stated to be safe and feasible [1], even though several publications report a substantial number of complications [2–4]. With evolving experience, various risk factors have been identified, including obesity, groin scarring, common femoral artery (CFA) morphology and tortuous iliac arteries [1, 5].

Many current devices successfully close percutaneous punctures of the CFA up to 8 Fr.: such as the Angio-Seal™ (St. Jude Medical, Minnetonka, MN, USA), Mynx™ (AccessClosure, Mountain View, CA, USA), and the Starclose™ device (Abbott Vascular, Redwood City, CA, USA). The Prostar XL™ device (Abbott Vascular) has been used in femoral arteries, after sheaths of 18 to 24 Fr., with high rates of procedural success [1]. Wound infections appear to be absent [3, 6, 7] or few (0.2 %) [8]. In contrast, open femoral access has wound infection rates varying from 6.4 % [9] to 7.3 % [7]. Also, a longer surgery and hospital stay have been reported [10–12]. In percutaneous access, secondary interventions were more commonly seen, compared to surgical cutdown [10, 11]. Still, in suitable patients, this seems to be the only device capable of closing a 20 Fr. percutaneous arterial access site.

Although research has been performed, comparing both techniques, a comparison of both techniques in one patient has never been performed prior to now. Risk factors (obesity, CFA morphology and tortuosity of the iliac arteries) will be equally divided in this study design. Therefore, postoperative complications will mainly depend on the technique used and on the diameter of the device implanted. Also, each patient will be able to compare the result of both techniques by subjective pain sensation or discomfort.

## Methods/Design

### Study design

In the current study, percutaneous femoral access is compared to open femoral access. Bilateral femoral access is required in each patient treated with a bifurcated EVAR. Therefore, each patient can serve as his/her own control. Randomization is performed for the caliber of the endovascular device (main device versus contralateral extension) that is introduced within the aorta.

The PiERO trial is designed as a randomized, controlled, nonblinded, multicenter superiority trial with two parallel groups and a primary endpoint of wound infection during the 30 days after surgery. Simple randomization will be performed concerning the diameter of the device component introduced in the artery, with a 1:1 allocation.

### Sample size calculation

The assumption has been made that a pEVAR is less likely to cause a surgical site infection (SSI) than an EVAR with surgical cutdown to the femoral artery. We estimated the number of patients needed in a superiority trial with an effect size of 90 % and a margin of 10 (alpha 5 %, power 80 %). Assuming an SSI incidence of 6.8 % (Table 1) in an open surgical femoral cutdown and of 0.1 % in pEVAR, where *p*1 = 0.068 and *p*2 = 0.001 and using the equation *n* = 8 × (*p*1(1 − *p*1) + *p*2(1 − *p*2))/(*p*1 − *p*2)^2^ [13], 120 patients are required to reach sufficient evidence and avoid a type 2 error (including a fall-out percentage of 5 %).

**Table 1 Tab1:** Wound complication rates mentioned in various studies

Studies	Surgical cutdown	Percutaneous access	Number of patients	*P* value	Research type
Johanning (2001) [8]	nm	0.2	489	-	retrospective
Nehler (2001) [3]	nm	0	189	-	systematic review
Eisenack (2009) [6]	nm	0	500	-	prospective
Zhong (2011) [7]	7.3	0	236	<0.01	retrospective
RIVM (2014)	6.4	nm	329	-	retrospective
Total:	6.8	0.1	1743		

*nm* not mentioned

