#### Secondary study parameter(s)

The number of wound complications in both groups will be compared as mentioned previously.

Patient characteristics will be controlled by multivariate analysis with respect to the duration of operation, left/right differences, preoperative bacterial colonization of the nose and the perineum, diabetes mellitus, body mass index, medication, smoking habits and device failure. Although identical groups are examined, we will be able to identify outliers.

Correlations between factors will be estimated using the Pearson correlation coefficient. Proportions of categorical variables are compared using Chi square and Fisher Exact tests, and means of continuous variables are compared using t tests.

The analysis of the primary endpoint (surgical site infection) will be based on an intention-to-treat principle by proportional hazards regression (visualized by Kaplan-Meier survival curves). Intention-to-treat implies that open access because of failed percutaneous access is not excluded from analysis but remains in the percutaneous group. Reasons why percutaneous access may not be successful are inability to obtain access to the arterial lumen with a needle, rupture of the threads of the Prostar XL™ device/2 Proglide™ devices, necessitating open repair and persistent bleeding despite successful use of the Prostar XL™ device/2 Proglide™ devices. The survival analysis is not affected by patient withdrawals (as they will be censored) provided that dropping out is unrelated to prognosis (Table 4). Other outcomes, such as VAS scores 2 weeks post-randomization, may be missing for patients who withdraw from the trial. We will actively seek out reasons for withdrawal and compare the reasons qualitatively.

**Table 4 Tab4:** Number of included patients in the participating centers

Participating center	Number of included patients
- University Medical Center Groningen	13 patients included
- Isala Hospital Zwolle	19 patients included
- Medical Center Leeuwarden	14 patients included
- Wilhelmina Hospital Assen	8 patients included
- Scheper Hospital Emmen	1 patient included
Total:	55 patients included

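### The sample size statement names an effect size of 90 % and a margin of 10, but its formula uses neither: 120 patients follow from 6.8 % versus 0.1 %, a 98.5 % relative reduction with no margin

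*Protocol article*

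**What the plan says.** The Protocol article, Sample size calculation, opens its justification with "We estimated the number of patients needed in a superiority trial with an effect size of" 90 %; the full specification reads "an effect size of 90 % and a margin of 10 (alpha 5 %, power 80" %). It then gives an open-access infection rate of 6.8 % and a percutaneous rate of 0.1 %, puts these into n = 8 × (p1(1 − p1) + p2(1 − p2))/(p1 − p2)², and concludes that "120 patients are required to reach sufficient evidence and avoid a type 2 error", including 5 % fall-out.

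Three other places bear on this:

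- Study design calls the trial a superiority trial in which each patient is his or her own control, so one patient gives one pair of groins.
- Statistical analyses, Primary study parameter(s), plans a McNemar test alongside proportional hazards regression. It does not say which version of McNemar.
- Secondary study parameter(s) sets the intention-to-treat rule: "open access because of failed percutaneous access is not excluded from analysis but remains in the percutaneous group".

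**The concern.** A sample size statement should let the reader see which effect the trial can detect. Here the sentence naming the target and the formula producing the number do not agree. The 90 % has no stated scale and the 10 has no unit. If the 10 means percentage points, it is larger than the whole open-access rate of 6.8 %, so no reduction from that rate could reach it. A margin also has no role in a plain superiority comparison of two rates.

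What is at stake is how the result is read. A reader who takes the 90 % as a relative reduction would believe the trial has 80 % power for it, when the calculation bought 80 % power for near-total elimination of infection.

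**Working it through.** **Inputs, all from Sample size calculation:** p1 = 0.068, p2 = 0.001, alpha 5 %, power 80 %, fall-out 5 %. The multiplier 8 approximates (1.96 + 0.84)² = 7.84, so a two-sided test is implied. After 5 % loss, 120 patients leave 120 × 0.95 = 114 pairs.

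**1. The plan's own figure.**
8 × (0.068 × 0.932 + 0.001 × 0.999)/0.067² = 8 × 0.064375/0.004489 = 114.7. Dividing by 0.95 gives 120.8; multiplying by 1.05 gives 120.5. The stated 120 reproduces to within rounding.

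**2. The effect those inputs imply.**
Difference: 6.8 − 0.1 = 6.7 points. Relative reduction: 0.067/0.068 = 98.5 %. The formula has no margin term and no separate effect-size term.

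**3. The 90 % read as a relative reduction (assumption).**
p2 = 0.1 × 0.068 = 0.0068. Then 8 × (0.063376 + 0.006754)/0.0612² = 149.8, so 150 evaluable patients; 149.8/0.95 = 157.7, so 158 with fall-out. Two-proportion power at this effect is 68.5 % with 114 and 70.7 % with 120.

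**4. Power of the McNemar test.**
Power was summed over the binomial number of discordant pairs, two-sided at 5 %, with the two groins of a patient independent. The discordant probabilities are p1(1 − p2) and p2(1 − p1). At the article's rates and 114 pairs, 114 × (0.068 × 0.999 + 0.001 × 0.932) = 7.85 discordant pairs are expected.

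| Rates | Pairs | Exact | Mid-p | Asymptotic |
|---|---|---|---|---|
| 6.8 % vs 0.1 % | 120 | 80 % | 89 % | 94 % |
| 6.8 % vs 0.1 % | 114 | 76 % | 87 % | 92 % |
| 6.8 % vs 0.68 % | 120 | 63 % | 74 % | 76 % |
| 6.8 % vs 0.68 % | 114 | 59 % | 71 % | 74 % |

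The continuity-corrected test matches the exact test to the precision shown. The versions differ because so few pairs are discordant. With all discordant pairs in one direction, the exact test needs six (2 × 0.5⁶ = 0.031), mid-p needs five (0.5⁵ = 0.031) and the asymptotic test needs four (√4 = 2 > 1.96).

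**5. Sensitivity to conversions (assumed rates).**
Suppose a share f of percutaneous accesses convert and then carry the open-access risk. The intention-to-treat rate is p2 = (1 − f) × 0.001 + f × 0.068.

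- f = 5 %: p2 = 0.00435, formula n = 133.7, power at 114 pairs 66 % exact to 82 % asymptotic.
- f = 10 %: p2 = 0.0077, formula n = 156.2, power at 114 pairs 57 % to 72 %.

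**The case against.** The strongest reply is that the number itself is sound. The formula and the two rates are printed, 120 follows from them, and the 90 % and the 10 may be left over from another calculation. There is a candidate: 90 % success in both groups, a 10-point non-inferiority margin and one-sided 5 % give 112 per group, or 112/0.95 = 118 with fall-out. That is close to 120, but it is a different hypothesis from the superiority trial described, so it may explain the phrase without rescuing it.

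The reply also limits the consequences. Three stronger readings are tempting, and the documents do not support them.

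- **That 120 patients are too few for the planned McNemar test because the formula is unpaired.** With p2 near zero almost every infection makes a discordant pair, so the paired requirement is similar or smaller. For 80 % power it is 86 pairs asymptotically, 118 by a Connor-type formula and 120 exactly. The one shortfall, 76 % at 114 pairs, belongs to the exact or continuity-corrected test, which the article does not name.
- **That the trial demonstrably lacks power for its stated effect.** This depends on reading the 90 % as a relative reduction, and also on independent groins. If every percutaneous infection occurred in a patient whose open groin was also infected, the extreme of positive correlation, power at 114 pairs for a 90 % reduction would be 70 % exact, 83 % mid-p and 92 % asymptotic.
- **That the open rate per groin is only half of 6.8 %.** The table titled "Wound complication rates mentioned in various studies" counts patients, but it does not say whether its rates are per patient or per groin, or how many cutdowns each patient had. Halving is an undocumented assumption and is not a shortfall in this plan.

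Nor does the article give a conversion rate or say how the cited series counted conversions, so step 5 stands only as sensitivity.

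**Conclusion.** The inconsistency stands without any assumption: the two figures offered as the planning target do not enter the calculation and do not match its inputs. It is more than clerical, because this is the article's only account of the effect behind the sample size.

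The size of the consequence is conditional. If the 90 % is a relative reduction from 6.8 % and the groins are independent, the formula falls short by about 35 evaluable patients (150 − 115), and every McNemar version is below 80 % at both 114 and 120 pairs. At 6.8 % versus 0.1 % there is no general failure of power. Sensitivity to a percutaneous rate above 0.1 % is real, but its amount rests on conversion rates that the article does not supply.

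**What to change.** In Sample size calculation:

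- Delete the 90 % and the margin of 10. State the planned effect as 6.8 % versus 0.1 % per groin: a 98.5 % relative reduction, superiority, no margin.
- In Primary study parameter(s), name the McNemar version. Report its power at 114 evaluable pairs (exact 76 %, mid-p 87 % or asymptotic 92 %), together with its power at a 90 % reduction (59 %, 71 % or 74 %), and state that independent groins are assumed.
- Optionally, add one line on sensitivity to conversions kept in the percutaneous group, labelled as an assumption: 66 to 82 % power at 5 % conversion and 57 to 72 % at 10 %, both at 114 pairs.
- Keep 120 patients.

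The cost is a few sentences and no extra patients. The power reported becomes specific to a named test and, for the exact version, slightly less favourable than the 80 % now printed.

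### The sample size section states an effect size of 90 % and a margin of 10, but the 120 patients follow from 6.8 % versus 0.1 %, a 98.5 % relative reduction

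*Protocol article*

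**What the plan says.** All of this is in one paragraph of the protocol article, under Sample size calculation.

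- Stated target: "We estimated the number of patients needed in a superiority trial with an effect size of 90" per cent, together with a margin of 10 that has no unit, and "alpha 5 %, power 80" per cent.
- Rates: "Assuming an SSI incidence of 6.8" per cent for open cutdown and 0.1 % for percutaneous access, both taken from the totals row of Table 1.
- Formula: n = 8 × (p1(1 − p1) + p2(1 − p2))/(p1 − p2)², with p1 = 0.068 and p2 = 0.001.
- Result: "120 patients are required to reach sufficient evidence and avoid a type 2 error", a figure described as "including a fall-out percentage of 5" per cent.

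Under Study design, both techniques are used in every patient, so that "each patient can serve as his/her own control". The Statistical analyses section names McNemar's test for the primary endpoint, alongside proportional hazards regression, and does not say which version of McNemar's test.

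**The concern.** The first sentence of the calculation says which effect the trial was sized for. The next sentence calculates the size from a different one. The rates in the formula amount to near-abolition of infection in the percutaneous groin, which is a larger effect than a 90 % reduction.

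The sample size statement tells a reader what a non-significant result would mean. As printed, it attaches 80 % power to a 90 % effect, while the calculation supports 80 % power only for 6.8 % against 0.1 %. The margin of 10 makes this worse: it suggests that some tolerance entered the design, yet the formula has no such term and the paragraph gives it no unit.

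**Working it through.** **Inputs.** p1 = 0.068, p2 = 0.001, multiplier 8, fall-out 5 %, alpha 5 %, power 80 % and 120 patients, all from the Sample size calculation section. Evaluable patients after fall-out: 120 × 0.95 = 114.

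**1. Reproducing the 120.**
- p1(1 − p1) = 0.068 × 0.932 = 0.063376
- p2(1 − p2) = 0.001 × 0.999 = 0.000999
- n = 8 × 0.064375 / 0.067² = 0.515 / 0.004489 = 114.7
- With fall-out: 114.7 / 0.95 = 120.8, or 114.7 × 1.05 = 120.5

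The stated 120 is reproduced to within rounding. The multiplier 8 is close to (1.96 + 0.842)² = 7.85, so the calculation is in effect two-sided at 5 % with 80 % power.

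**2. The effect in those inputs.**
- Absolute difference: 6.8 − 0.1 = 6.7 percentage points
- Relative reduction: 1 − 0.001/0.068 = 98.5 %
- Infection-free proportions: 93.2 % and 99.9 %

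None of these is 90 %, and none is a margin of 10.

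**3. If the 90 % is a relative reduction.** This reading is an assumption. It gives p2 = 0.068 × 0.10 = 0.0068.
- p2(1 − p2) = 0.0068 × 0.9932 = 0.006754
- n = 8 × (0.063376 + 0.006754) / 0.0612² = 0.56104 / 0.0037454 = 149.8, so 150 evaluable patients
- With fall-out: 149.8 / 0.95 = 157.7, so 158 patients, 38 more than stated

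**4. Two-sided power by the same approximation.** Power = Φ(d/SE − 1.96), with d = p1 − p2 and SE = √[(p1(1 − p1) + p2(1 − p2))/n].

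| Percutaneous rate | n = 114 | n = 120 |
|---|---|---|
| 0.1 % (rate used) | 80.5 % | 82.5 % |
| 0.68 % (90 % reduction) | 69.4 % | 71.6 % |

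For 0.68 % at n = 114: SE = √(0.07013/114) = 0.0248, d/SE = 2.47, and Φ(0.51) = 69 %.

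**5. Two-sided McNemar power, by enumeration over discordant pairs.** With independent groins, the discordant probabilities are p1(1 − p2) and p2(1 − p1). Maximum positive correlation means that every percutaneous infection occurs in a patient whose open groin is also infected.

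| Scenario | Pairs | Exact | Mid-P | Uncorrected |
|---|---|---|---|---|
| 0.1 %, independent | 114 | 76 % | 87 % | 92 % |
| 0.68 %, independent | 114 | 59 % | 71 % | 74 % |
| 0.68 %, independent | 120 | 63 % | 74 % | 77 % |
| 0.68 %, maximum correlation | 114 | 70 % | 83 % | 92 % |
| 0.68 %, maximum correlation | 120 | 75 % | 86 % | 94 % |

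**The case against.** **The 90 % is undefined.** Set beside a margin of 10, it need not be a relative risk reduction; it could be a success proportion with a 10-point margin. This stands. On another meaning, the 0.68 %, the 158 patients and the power shortfall have no basis in the document. The mismatch remains, however. As an absolute difference, 90 % cannot fit rates of 6.8 % and 0.1 %. As an infection-free proportion, it matches neither 93.2 % nor 99.9 %.

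**The effect used is printed in the same paragraph.** The rates, formula and result are all there, and they agree with each other. This also stands, and it is why the fault lies in the description and not in the arithmetic. A reader might infer that 120 is the wrong number or that the trial must recruit 158. The documents do not support that, because 120 is correct for the rates the protocol chose.

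**The shortfall depends on the test.** A reader might take the exact and mid-P results at 114 pairs and state a flat type II error of 29-41 %. That goes too far for three reasons:
- The protocol does not name a version of McNemar's test, and the uncorrected one gives 74 % power, a 26 % error.
- Part of the exact test's loss has nothing to do with the 90 %: at the plan's own rates and 114 pairs it reaches only 76 %.
- The paired figures assume independent groins, although the design rests on shared patient risk factors. At maximum correlation, mid-P and uncorrected power exceed 80 %.

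**A one-sided test would nearly close the gap.** One-sided power for 6.8 % to 0.68 % is about 79 % at 114 and 81 % at 120. But a one-sided 5 % calculation would use a multiplier of 6.18 and give 88.7 patients before fall-out for the stated rates. The printed 8 does not fit that.

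**Non-significance does not rule out an effect.** That is true at any power, and a confidence interval is the better guide. It limits the harm, but the design target is still misdescribed.

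**Conclusion.** The concern holds as an error in the stated design effect. The 90 % and the margin of 10 are undefined and unused, and the 80 % power belongs to 6.8 % against 0.1 %. That much needs no assumption.

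The loss of power is conditional. It requires reading the 90 % as a relative reduction and keeping the two-sided test that the multiplier implies. By the plan's own formula, power is then 69-72 % with 114 to 120 patients. For McNemar's test, the result also depends on the version chosen and on within-patient correlation, for which the protocol gives no value. With independent groins all three versions stay below 80 %; with strong positive correlation, mid-P and uncorrected power can exceed it.

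Severity: should-fix. The 120 itself is not in error, and no endpoint, analysis or trial conduct is affected.

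**What to change.** In the Sample size calculation section, delete both the 90 % effect size and the margin of 10. In their place, state the target actually used. For example: *The sample size is based on a reduction in SSI incidence from 6.8 % with open access to 0.1 % with percutaneous access (6.7 percentage points, a 98.5 % relative reduction), with alpha 5 % and power 80 %. For a 90 % relative reduction (to 0.68 %), the same formula gives about 69 % power with 114 evaluable patients.*

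Keep the rates, formula, fall-out allowance and 120 patients as they are. The added power statement is true whatever the 90 % was meant to express.

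The cost is a reworded sentence and one added sentence. The protocol loses the claim of 80 % power for a 90 % effect, and no patients are added.

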### Statistical analyses

#### Primary study parameter(s)

The occurrence of SSIs in both groups will be compared with a McNemar’s test and proportional hazards regression. Only two measuring points will be defined, but wound complications are expected to emerge also between these measuring points. A Kaplan Meier curve may be used to log incidences according to time. Both groups will be compared using the log rank test.

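### The 120 patients and 80 % power are derived for two independent groups, not for the paired McNemar test the protocol names; at 114 evaluable pairs that test has 76 % to 92 % power, depending on a version not fixed

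*Protocol article*

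**What the plan says.** Under Sample size calculation, the protocol article describes the number needed "in a superiority trial with an effect size of 90" % and a margin of 10, with "alpha 5 %, power 80" %. It proceeds by "Assuming an SSI incidence of 6.8 % (Table 1) in an open surgical femoral cutdown and of 0.1 % in pEVAR", and by "using the equation *n* = 8 × (*p*1(1 − *p*1) + *p*2(1 − *p*2))/(*p*1 − *p*2)^2". The result is that "120 patients are required to reach sufficient evidence and avoid a type 2 error", "including a fall-out percentage of 5" %.

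Under Study design, the comparison is within the patient: "each patient can serve as his/her own control". Under Primary study parameter(s), infections in the two groups are to be "compared with a McNemar’s test and proportional hazards regression". No version of McNemar's test, discordant proportion or within-patient correlation is given.

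**The concern.** The equation adds two separate binomial variances and has no covariance or discordance term, so it gives the size per group for two independent groups. McNemar's test uses only patients infected in one groin and not the other. The stated 80 % was therefore not derived for the named test in this design.

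At the assumed rates about 8 discordant patients are expected. With so few, the versions of McNemar's test differ in what they call significant. The true power may lie on either side of 80 %, and the same four or five infections could be significant or not according to the version run.

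The same paragraph also announces two parameters that the calculation never uses, so the effect the trial is meant to detect is unclear.

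**Working it through.** **Inputs (Sample size calculation).** p1 = 0.068 (open), p2 = 0.001 (percutaneous), alpha 5 %, power 80 %, fall-out 5 %, N = 120. Sidedness is not stated. The factor 8 is close to (1.96 + 0.84)² = 7.84, so two-sided is taken. Evaluable pairs: 120 × 0.95 = 114.

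**Reproducing the plan.**
- n = 8 × (0.068 × 0.932 + 0.001 × 0.999)/0.067² = 8 × (0.063376 + 0.000999)/0.004489 = 114.7.
- With fall-out: 114.7 × 1.05 = 120.5, or 114.7/0.95 = 120.8.

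The 120 reproduces, give or take rounding.

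**Paired set-up.** Assumption: infections in a patient's two groins are independent.
- Infected in the open groin only: 0.068 × 0.999 = 0.067932.
- Infected in the percutaneous groin only: 0.001 × 0.932 = 0.000932.
- Discordant proportion ψ = 0.068864; difference d = 0.067.
- Expected discordant pairs among 114: 114 × 0.068864 = 7.85.

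**Paired normal approximation.**
- n = (1.96√ψ + 0.8416√(ψ − d²))²/d² = (0.5143 + 0.2135)²/0.004489 ≈ 118 pairs, against 115 from the plan's equation.
- Power at 114 = Φ((0.067√114 − 1.96√ψ)/√(ψ − d²)) = 78.6 %.

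**Enumeration over discordant counts, two-sided 5 %, 114 pairs.** The last column gives the fewest discordant pairs, all in one direction, that reach p < 0.05.

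| McNemar version | Power | Smallest significant one-sided split |
|---|---|---|
| Exact | 76.4 % | 6:0 (p = 0.031; 5:0 gives 0.0625) |
| Continuity-corrected | 76.4 % | 6:0 (p = 0.041) |
| Mid-p | 86.8 % | 5:0 (p = 0.031) |
| Uncorrected chi-square | 92.3 % | 4:0 (p = 0.046) |

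**Sensitivity to the assumption.** At these rates the probability that both groins are infected can only lie between 0 and 0.001, so ψ lies between 0.067 and 0.069. Over that range the exact test has 76.3 % to 78.3 %.

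**Sensitivity to fall-out.** With all 120 evaluable the exact test has just over 80 %. It first reaches 80 % at 120 evaluable pairs, and 120/0.95 = 126.3, so 127 enrolled.

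**Where the shortfall comes from.** In two truly independent groups of 114 at the same rates, Fisher's exact test has 76.3 % power, practically the same as exact McNemar.

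**Type I error at 114 pairs.** The maximum over discordant proportions of 1 % to 29 % is 3.2 % (exact), 4.6 % (mid-p) and 5.3 % (uncorrected).

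**The unused parameters.** The rates used imply a relative reduction of (0.068 − 0.001)/0.068 = 98.5 %, and the equation contains no margin. If, as an assumption, 90 % means a relative reduction, then p2 = 0.0068. The plan's own equation then gives 149.8, so 150, and 149.8/0.95 = 157.7, so 158 with fall-out.

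**The case against.** The strongest reply is that the wrong equation does little harm. With p2 almost zero, the paired and independent requirements nearly coincide (about 118 v 115). The Fisher comparison shows that a conservative test loses the same power without any pairing. This stands: a reader might infer that ignoring the pairing cost the trial its power, and the figures do not support that.

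Next, 76 % belongs to a version the protocol never chose, and two versions comfortably exceed 80 %. The version may be left to a fuller document. That also stands, so its absence is not itself the error. The Sample size calculation does, however, state an equation and a power in full, and that power is neither derived for the named test nor equal to any of its versions at 114 pairs.

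Third, McNemar's test is not the only primary analysis. Proportional hazards regression and the log-rank test are named beside it, and the section on secondary parameters ties the intention-to-treat analysis of the primary endpoint to proportional hazards regression. No power was computed for those methods here, so one cannot claim that the McNemar version alone decides the trial.

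Finally, a reader might take the 90 % as an announced relative reduction and conclude that the trial is clearly underpowered. The protocol does not say what the 90 % measures, and it explicitly fixes p2 at 0.001. The 150 and 158 show why the phrase needs explaining; they do not establish an underpowered design.

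**Conclusion.** The concern holds in a limited form. The sample size is derived for a design and test other than those described, and the stated 80 % does not match the named test at 114 evaluable pairs: 76 % (exact or corrected), 87 % (mid-p) or 92 % (uncorrected). This rests on the plan's rates, a two-sided 5 % level, 5 % fall-out and independence of the groins. The last assumption matters little, since the exact test stays within 76 % to 78 % whatever the correlation.

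The shortfall is modest, applies only to the conservative versions, disappears for them if all 120 patients are evaluable, and comes mainly from small counts. The 90 % and the margin of 10 are unexplained and unused. The point is worth correcting because the power statement is one the trial relies on, but it does not show that 120 patients are too few.

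**What to change.** In the Sample size calculation:

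- Replace the independent-groups equation with a paired (McNemar) calculation based on the discordant proportions, stating the assumed within-patient correlation.
- Name the McNemar version for the primary comparison before analysis, and restate its power for 120 enrolled and 114 evaluable pairs: about 76 % for the exact or continuity-corrected test. Mid-p is one option, at about 87 % with a type I error of at most 4.6 % at 114 pairs.
- Delete the effect size of 90 % and the margin of 10, or define them and reconcile them with the rates used.

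The cost is one reworded paragraph and one line on the test. No added enrolment is required at the stated rates. The downside is a slightly less favourable stated power if the exact or corrected test is chosen. If the 90 % turns out to be the intended relative reduction, the number needed would have to be recalculated.
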